#### Number of New Carious Teeth

An oral examination will be conducted at baseline (before the start of the intervention) and at the end of the 2-year study period by researchers using the NOHPS protocol, which was based on the World Health Organization (WHO) recommendation published in 2013 [19]. The number of new decayed, missing (due to caries), and filled posterior deciduous teeth (dmft), as well as the number of decayed, missing (due to caries), and filled first permanent molars (DMFT) will be recorded. The dmft and DMFT caries assessment is chosen to ensure consistency with the assessment used by the OHD Ministry of Health Malaysia.

#### Oral Health-Related Quality of Life Improvement

The OHRQoL improvement will be measured using the ECOHIS questionnaire. The ECOHIS questionnaire is a specific instrument developed by Pahel et al in 2007 to assess the perception of parents on OHRQoL of preschool children. It has 13 items, distributed between 2 sections, namely the Child Impact Section and the Family Impact Section. The Child Impact Section has 4 domains (child symptom, function, psychological, and self-image or social interaction); and the Family Impact Section has 2 domains (parent distress and family function). Responses are recorded using a 5-point Likert scale to record how often an event has occurred where 0=never, 1=hardly ever, 2=occasionally, 3=often, 4=very often, and 5=don’t know [20]. The ECOHIS has been validated on a Malaysian population and was found to have high validity (Cronbach alpha=.83) and high reliability (kappa=.95) in assessing the impact of oral disorders or conditions on the quality of life of urban preschool children age 4 to 6 years old as reported by Hashim et al [21].

The ECOHIS questionnaire will be completed by the parents in both the intervention and control groups at baseline and at the end of the 2-year follow-up period. Based on the responses, the ECHOIS score as prescribed by Hashim will be computed. The ECOHIS score at the end of the 2-year follow-up will be used to assess the improvement of OHRQoL of the children in both intervention and control groups.

#### Costs of Dental Home Visits and Educational Leaflets

The DHVs cost data will include the cost of dental home visitors, telephone calls, administration costs, and travelling costs of dental home visitors. The costs of the dental home visitors will be calculated according to the average salary of a dental nurse; the costs of the telephone calls used to make appointments for DHVs will be estimated according to the fees of prepaid phone number; and the travelling costs of the dental home visitors will be estimated by the average travel allowance per day in the Selangor area. The administration cost will include the costs of paper, stationary, and photocopies used for the informed consent forms and letters to authorities, as well as the training cost for delivering intervention. As the ELs used in the study will be obtained from existing Ministry of Health leaflets which are most relevant to the study objectives, the ELs cost in this study will be estimated by using the market price for purchase of leaflets, staff salaries, telephone calls, travelling allowances, and administration costs.

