## Methods

### Study Design

This is a CEA of DHVs to families of young children for caries prevention compared to young children receiving oral health information in the form of ELs over a period of two years. For the CEA, the study adopted a societal perspective, which has been suggested as the most appropriate and comprehensive perspective [14]. In this perspective, all types of resources that are of value to society will be included in analyzing the costs; such as cost to the patient, cost to the provider or institution, and indirect costs because of loss of productivity.

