### Control Group

The control group will receive ELs that will be delivered by hand at 6-month intervals for the 2-year study period by the dental home visitors.

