#### Costs of Dental Treatment

The cost data for dental treatment incurred by the families will be obtained from the recorded dental visit diary completed by the parents. The dental visit diary will be created to record every dental visit made during the study period and checked by the researchers every six months until the end of the study period. The information recorded in the diary will capture the reason for the dental visit, the type of dental clinic visited, the dental treatment or procedure conducted, the time spent at the dental clinic, the time spent travelling to and from the dental clinic, the total cost of the dental treatment or procedure, the cost of travelling to and from the dental clinic, the person who brought the child to the dental clinic, and the number of parents’ days off used to bring the child to the dental clinic. The use of dental visit diary has been reported to be suitable for self-completion by the parents [22].

The dental visit diary will be created according to an annotated cost questionnaire as proposed and validated by Thompson and Wordsworth for the UK Health Economics Research Unit [22]. It will be translated to Bahasa Malaysia using the forward and backward translation process. It will be pretested to assess its relevance and ease of understanding by the potential participants in the context of the communities included in the study.

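### The costing rules do not deliver the declared societal perspective: trial paperwork counts as programme cost, parents' home-visit time is left out, and treatment cost is taken only as incurred by families

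*Protocol article*

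**What the plan says.** The Study Design section of the protocol article, like the Abstract, takes a societal perspective. It commits to counting "all types of resources that are of value to society will be included in analyzing the costs; such as cost to the patient", and also "cost to the provider or institution, and indirect costs because of loss of productivity".

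Three later sections turn this into cost items.

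- **Costs of Dental Home Visits and Educational Leaflets.** For the home visits: "The DHVs cost data will include the cost of dental home visitors, telephone calls, administration costs, and travelling costs of dental home visitors". Administration is then defined: "The administration cost will include the costs of paper, stationary, and photocopies used for the informed consent forms and letters to authorities". Training to deliver the intervention falls under the same item. The educational leaflets (ELs) are costed from the "market price for purchase of leaflets, staff salaries, telephone calls, travelling allowances, and administration costs", so an administration item appears on the leaflet side as well.
- **Costs of Dental Treatment.** Here one source is named: "The cost data for dental treatment incurred by the families will be obtained from the recorded dental visit diary completed by the parents". Diary entries cover clinic type, procedure, a total treatment cost, time at the clinic, travel time and cost, and the days parents took off.
- **Cost-Effectiveness Analysis.** The ICER numerator is the difference between arms in dental treatment cost. Sensitivity analysis is ruled out, partly on the ground that the costs are real-world data.

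The Outcome Measures section gives a second ratio: DHV and EL cost divided by the number of children prevented from developing caries. It does not say that control-arm cost is subtracted.

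**The concern.** A societal analysis should count every resource that the programme uses or saves, whoever bears it, and nothing that exists only because a trial is being run. The costing sections depart from this in three ways.

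1. Consent paperwork and correspondence with authorities would not exist in a routine DHV service, yet they are booked as programme cost.
2. Parents must be at home for the visits, so the intervention uses their time. That time is not listed. Their time for clinic attendance is recorded, so parent time is counted where DHVs may save it and not where DHVs use it.
3. Provider cost is promised, but the only stated source for treatment cost is what families incur, reported by parents.

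At stake is whether the ratios mean what the protocol says they mean to a decision-maker. No planned analysis would show the effect of any of the three.

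**Working it through.** The article gives no prices, so no incremental cost can be computed. The check compares the cost items across sections and sizes what can be sized.

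**Inputs**
- Incidence 5% (intervention) and 20% (control), and a target effective sample of 300, so 150 per arm: Sample Size and Randomization.
- Visits of about 30 minutes by two visitors: The Intervention.
- Follow-up visits at months 6, 12 and 18: Follow-Up 6-Monthly Visits. A baseline home visit: Baseline Data. This gives 3 advice visits, or 4 if advice is also given at baseline.
- Assumption: one parent is present at each visit.

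The only design figure stated, a minimum of 176 subjects, reproduces: 5% versus 20%, two-sided 0.05, 80% power, with continuity correction, gives 88 per arm, 2 × 88 = 176. This confirms the reading of the incidence inputs. The costing point does not depend on it.

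**(a) Trial paperwork.** Let it cost c per child.
- Difference in programme cost between arms, if c is the same in both: c − c = 0. Administration is also listed for the leaflets, so this is plausible.
- ICER as defined under Cost-Effectiveness Analysis: the numerator is treatment cost only, so c does not enter.
- Outcome Measures ratio, if its numerator is the full intervention-arm cost: children prevented = 150 × 0.20 − 150 × 0.05 = 30 − 7.5 = 22.5. Added to the ratio: 150c / 22.5 = 6.7c per child prevented.

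**(b) Parent time at home visits.**
- Per family: 3 × 0.5 h = 1.5 h, or 4 × 0.5 h = 2 h.
- Per 150 families: 150 × 1.5 = 225 h to 150 × 2 = 300 h.
- Contact time of the two visitors: 2 × 1.5 = 3 to 2 × 2 = 4 person-hours per family. Parent time is therefore half of the visitor contact time that is costed.
- Control homes are also visited every 6 months for leaflets and diary checks. The between-arm difference is 1.5 to 2 h less whatever time control parents spend at those visits, so these figures are upper bounds.

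**(c) Provider share of treatment cost.** Let s be the share of treatment cost that families do not bear, assumed equal in both arms. If the diary captures only the family's payment, the recorded difference is (1 − s) times the true difference. At s = 0 nothing is lost, at s = 0.5 half is lost, and at s = 1 all of it is lost. The documents give no basis for choosing s. The sign of the true difference is not fixed in advance either: DHVs may prevent treatment, but The Intervention section also has visitors explain the need for check-ups and how to reach local services.

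**The case against.** The strongest reply is that none of this shows the incremental cost to be wrong. Much of it stands.

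- **The paperwork is minor.** It is paper and copying, it cancels between arms if equal per child, and it never enters the ICER as defined. This is correct. What remains is a misclassification that affects the Outcome Measures ratio under one reading of its numerator.
- **Parent time is not ignored altogether.** A reader might infer that parents' visit time in general is left out. The diary refutes that for clinic visits; only home-visit time is unlisted. Home-visit time is also outside the ICER numerator as written.
- **Provider cost is promised, and the diary could support it.** The diary asks for a total treatment cost, not expressly the family's payment, and records clinic type and procedure. A condensed article may also leave unit-cost sources to the full protocol. That is fair, and a reader should not infer that unbilled treatment is certainly valued at zero, since nothing is said about subsidy. But the section is not silent on source: it names cost incurred by families, as reported by parents, who would normally know only what they paid.
- **Leaflet delivery.** Control families receive "ELs that will be delivered by hand at 6-month intervals for the 2-year study period by the dental home visitors", and a reader might infer that sharing delivery cost between arms hides the true cost of DHVs. It does not. Cancelling shared cost is correct arithmetic for the two arms compared. Costing leaflets without home delivery would pair one comparator's cost with another's effect. Any multiple put on it would need a trip length that the documents do not give.

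The treatment-only ICER numerator and the programme-cost-only ratio under Outcome Measures also disagree with each other. That is a separate and larger matter, and resolving it would not repair the three items here.

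**Conclusion.** The point holds in a limited form: followed as written, the costing sections do not deliver the societal perspective declared in the Abstract and Study Design. A reader might go further and conclude that the incremental cost is biased in a known direction. The documents do not support that, because there are no prices, the three items need not push the same way, and two of them lie outside the ICER as defined.

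By item:
- Paperwork: wrongly classified and probably small. The 6.7-fold multiplier rests on the planning incidences, 150 per arm, and no subtraction of control-arm cost.
- Parent home-visit time: a real omission of at most about 1.5 to 2 h per intervention family, assuming one parent present. The asymmetry with clinic time favours DHVs in any analysis that includes both programme cost and clinic time.
- Provider share of treatment cost: size unknown, but potentially the most important of the three, because it bears on the whole ICER numerator.

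The point is worth acting on because the corrections are specific and cheap, and because no sensitivity analysis is planned that would reveal the effect.

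**What to change.** Under Costs of Dental Home Visits and Educational Leaflets:
- Remove consent-form and authority-letter costs from programme cost in both arms. Keep training.
- Add parent time per home visit, valued at the same wage as is applied to parents' clinic time. Treat any time control parents spend at leaflet visits in the same way.

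Under Costs of Dental Treatment:
- Value each diary-recorded procedure at a provider unit cost by clinic type. Count family payments once, so that a fee is not added on top of a unit cost that already covers it.

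A scenario in which leaflets are costed without home delivery is optional. It would speak to roll-out, not to the comparison made in this trial.

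Cost: a unit-cost table has to be obtained from the collaborating Oral Health Division. The diary already records procedure and clinic type, the length of a home visit is stated, and removing the paperwork needs no new data. Randomisation, the intervention and the clinical examinations are unaffected, and the article reports that recruitment is still under way.

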#### Costs of Dental Treatment

The cost data for dental treatment incurred by the families will be obtained from the recorded dental visit diary completed by the parents. The dental visit diary will be created to record every dental visit made during the study period and checked by the researchers every six months until the end of the study period. The information recorded in the diary will capture the reason for the dental visit, the type of dental clinic visited, the dental treatment or procedure conducted, the time spent at the dental clinic, the time spent travelling to and from the dental clinic, the total cost of the dental treatment or procedure, the cost of travelling to and from the dental clinic, the person who brought the child to the dental clinic, and the number of parents’ days off used to bring the child to the dental clinic. The use of dental visit diary has been reported to be suitable for self-completion by the parents [22].

The dental visit diary will be created according to an annotated cost questionnaire as proposed and validated by Thompson and Wordsworth for the UK Health Economics Research Unit [22]. It will be translated to Bahasa Malaysia using the forward and backward translation process. It will be pretested to assess its relevance and ease of understanding by the potential participants in the context of the communities included in the study.

### Data Collection Procedure

#### Standardization

Standardization and calibration training will be carried out by the OHD Ministry of Health Malaysia for the researchers in this project to ensure the reliability of the measurements in oral examination at the baseline and at the end of the 2-year follow-up period. The training is carried out in order to achieve the following outcomes:

Uniform interpretation, understanding, and application of recording instructions and criteria.Standardization and calibration of chosen examiners (researchers) against the benchmark examiner (OHD personnel).Reasonable consistency with minimal inter- and intraexaminer variability.Familiarization with survey forms, field procedures, and equipment to be used [23].

#### Baseline Data

The baseline clinical data for all study participants will be based on the oral examination to be carried out at the kindergarten for all children with the parents’ consent. This examination will be conducted by researchers who have successfully attended the standardization training session. Oral examination will use a disposable mouth mirror. Caries assessment will be based on visual inspection, without invasive probing, and is diagnosed at the cavitation stage. Both primary and permanent teeth will be examined and if a permanent and a primary tooth occupy the same space, then only the status of the permanent tooth will be recorded. Caries assessment will adhere closely to the NOHPS criteria [17], which has been modified in 2013 from the WHO recommendations [21]. It is important to note that the WHO uses alphabets to denote caries status for primary teeth, however, NOHPS protocol uses numeral for both primary and permanent teeth. Hence, in this study, the following coding will be used: Sound teeth=0 (instead of A), Caries=1 (instead of B), Filled with caries=2 (instead of C) and Filled no caries=3 (instead of D). The teeth examination will begin from upper right to upper left and lower left to lower right quadrant and a tooth will be considered present when any part of it is visible [19,23]. No radiographs will be taken, and no treatment will be provided. Children who have been assessed with obvious caries will be advised to visit a dental clinic for further assessment and for treatment if necessary.

Baseline DHVs will be carried out and the parents in both the intervention and control groups will receive the ECOHIS questionnaire and a dental visit diary. The baseline ECOHIS questionnaire will be filled by the parents during the visit and returned to the researchers. The dental visit diary will be maintained by the parents and the research team will check the diary every 6 months. Parents will be informed to complete the diary every time their children visit the dental clinic.

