## Introduction

In Malaysia, 86% of rural and 69% of urban preschool children have experienced dental caries, most of which remain untreated [1]. The dental treatment cost in young children is high due to the need for treatment under general anesthesia or sedation, therefore causing significant economic and social burdens on the families [2,3]. In 2012, nearly 4000 children in Malaysia were referred to hospital pediatric dental services because of dental caries [4].

Recent research has reported the effectiveness of dental home visits (DHVs) in preventing the development of caries in young children. The American Academy of Pediatric Dentistry describes DHVs as an ongoing relationship between the dentist and their patient, providing all aspects of a preventive oral health care program in the presence of the parents at home [5,6]_._ This concept has been reported to result in a sustainable oral health behavioral change as the child is more likely to receive appropriate preventive and routine oral health care, thereby reducing the risk of preventable dental disease [7]. In addition, DHVs have the advantage of providing a personalized preventive intervention based on a child’s needs [8].

A study reported in 2013 by Plonka et al showed that oral health education for children through home visits significantly reduced the rate of development of early childhood caries (ECC) compared to those who were contacted via telephone [9]. The results of this study showed the benefit of personal contact in home visits for delivery of oral health education, and this significantly reduced the number of children who developed ECC [9].

Other studies have investigated the cost-effectiveness of DHVs in caries prevention. One such example is a study which investigated the benefit-cost and cost-effectiveness of a long term dental health program for prevention of ECC in infants through home visits, and this study showed favorable results [10]. In a separate study, a home-visit intervention for ECC was found to be more cost-effective than a telephone intervention delivery mode, contributing significant cost savings to the public health care system [11].

Educational leaflets (ELs) are one of the materials commonly used in oral health promotion programs, which reinforce oral health education messages and are frequently used for the benefit of dental patients to complement communication with the dentist [12,13].

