Cost-effectiveness analysis (CEA) is widely used to inform decision-makers about the value of new health programs and interventions. CEA is the most commonly used technique for economic evaluation and it estimates the costs and effects of health interventions and sums up the results in a cost-effectiveness ratio [14].

Given the high prevalence of dental caries in Malaysia, and the availability of effective DHVs and ELs material to support oral health promotion, the rationale of this study is to identify effective and cost-effective behavioral interventions to promote oral health and reduce oral health disparities in the population [1,7,8,12,13]. Health behaviors and lifestyles can influence both the oral and general long-term health of the population which can have economic and social consequences [15]. Furthermore, this is the first reported study of DHVs in Malaysia and an economic evaluation in this area is needed to estimate the value of the outcomes received for the expenditures spent on this intervention.

The aim of this study is to evaluate the cost-effectiveness of DHVs and oral health information in the form of ELs in preventing new caries development in young children, compared to those receiving only ELs over a period of 2 years. The specific objectives are:

To determine the cost of DHVs and ELs for prevention of new caries per child compared to the cost for a child only receiving oral health information through ELs for prevention of new caries after a 2-year follow-up.To determine the cost of DHVs and ELs in improving the oral health-related quality of life (OHRQoL) for one child compared to the cost of only ELs in improving the OHRQoL for one child after a 2-year follow-up.To compare the cost of dental treatment incurred and all associated expenditures among children receiving DHVs and ELs and those receiving only ELs over 2 years.

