## Discussion

The cost of dental treatment in young children is high due to the severity of the caries developed which can require an aggressive treatment, as well as the need for general anesthesia or sedation. Children who receive treatment under general anesthesia frequently require further hospitalization for new lesions, some as soon as 6 months after the first general anesthesia. Clearly, existing health services need to be supplemented with a population-based approach to promote child oral health. This is the first study of this intervention in Malaysia, and economic evaluation in this area is crucial to estimate the value of the outcomes received for the expenditures spent on this intervention. This study will provide information on the cost and effectiveness of DHVs in caries prevention of young children in Malaysia.

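### Family costs and parent days off are recorded only when the child attends a dental clinic, which is narrower than the promised societal perspective and probably understates any saving from the home visits

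*Protocol article*

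**What the plan says.** The Abstract (Methods) and *Study Design* commit the cost-effectiveness analysis to a societal perspective, covering costs to the patient, costs to the provider and indirect costs from lost productivity. The third specific objective in the Introduction is "To compare the cost of dental treatment incurred and all associated expenditures among children receiving DHVs and ELs" and those receiving leaflets only.

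Family costs come from one instrument, described under *Costs of Dental Treatment*: "The dental visit diary will be created to record every dental visit made during the study period". *Baseline Data* gives the instruction to parents: "Parents will be informed to complete the diary every time their children visit the dental clinic". The listed fields include "the type of dental clinic visited, the dental treatment or procedure conducted", "the total cost of the dental treatment or procedure, the cost of travelling to and from the dental clinic", and "the number of parents’ days off used to bring the child to the dental clinic". Researchers check the diary every 6 months in both groups and collect its contents at 2 years.

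No other source of family cost is named. *Costs of Dental Home Visits and Educational Leaflets* covers only the cost of delivering the two programmes.

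**The concern.** Both the trigger and the productivity field depend on a clinic visit, while the perspective does not. A parent who stays home with a child in pain, buys medicine, or goes to a doctor or emergency department without seeing a dentist bears a cost that society values, and no entry is prompted. The Introduction says of preschool caries "most of which remain untreated", so losses without a visit may be common.

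The gap may also differ between arms. *The Intervention* includes advice on regular check-ups and on how to reach local services, so home visits may raise attendance, and the days off for that attendance are recorded in full. *Sample Size and Randomization* expects more new caries in the control group, so losses from untreated disease would be commoner there, and those are not recorded. Both effects push the recorded productivity comparison against the home visits.

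*Cost-Effectiveness Analysis* rules out sensitivity analysis on the ground that the cost data are real-world data. That reason presumes that the data cover the costs in scope, and no stated analysis would reveal the gap.

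**Working it through.** The protocol gives no productivity figure to reproduce. The only figures borrowed from it are the new-caries rates of 5% (intervention) and 20% (control). The sample size built on them does reproduce (88 per arm, 176 in total, two-sided 5% level, 80% power, continuity correction), but nothing here depends on it.

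**Scope check**

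| Loss | Prompts a diary entry? | Field listed? |
|---|---|---|
| Day off to take the child to a dental clinic | Yes | Yes |
| Hospital dental procedure and its charge | Can be entered as a dental visit | Yes: clinic type, procedure, total cost |
| Medicine supplied at a dental visit | Yes | Can fall within total cost |
| Inpatient stay as such | Unclear | No |
| Day off for a dental problem, no visit | No | No |
| Doctor or emergency care | No | No |
| Medicine bought without a visit | No | No |

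**Illustration A.** Assumptions, none from the protocol:
- 60% of affected children are untreated in both arms;
- 1 parent day is lost per treated child and d days per untreated child;
- home visits add a proportion x of children attending a check-up, at 0.5 day each.

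Days per child:
- Recorded, control: 0.20 × 0.40 × 1 = 0.08
- Recorded, intervention: 0.05 × 0.40 × 1 + 0.5x = 0.02 + 0.5x
- Recorded saving: 0.06 − 0.5x
- Saving missed by the diary: (0.20 − 0.05) × 0.60 × d = 0.09d
- Full saving: 0.06 + 0.09d − 0.5x

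With d = 1 the full saving is 0.15 − 0.5x. At x = 0.10 the diary shows 0.01 saved against a full 0.10, with no reversal. At x = 0.30 it shows 0.09 lost against a full saving of 0.

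The sign reverses when the recorded saving is negative and the full saving positive, that is for x between 0.06/0.5 = 0.12 and (0.06 + 0.09d)/0.5:

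| d | Upper limit of x | Reversal window |
|---|---|---|
| 1 | 0.15/0.5 = 0.30 | 12 to 30 points |
| 0.5 | 0.105/0.5 = 0.21 | 12 to 21 points |
| 0.25 | 0.0825/0.5 = 0.165 | 12 to 16.5 points |

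**Illustration B.** Other assumptions: 2 days per untreated child, 1 day per treated child, 0.5 day per check-up; in control, 40% of affected children treated and 10% of children attending a check-up. Differences are intervention minus control, in days per 100 children.

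| Intervention arm: treated / check-ups | Diary | Full |
|---|---|---|
| 40% / 10% (same as control) | −6 | −24 |
| 60% / 30% | +5 | −15 |

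First row: diary (2 + 5) − (8 + 5) = −6; the unrecorded days are 5 × 0.6 × 2 = 6 against 20 × 0.6 × 2 = 24, so the full difference is −6 + 6 − 24 = −24. Even with equal attendance the diary shows a quarter of the assumed saving. Over 40% to 80% treated and 10% to 50% check-ups in the intervention arm, the diary difference runs from −6 to +16 and the full difference from −26 to −4.

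**The case against.** The strongest reply is that the gap is narrower than it looks and that its direction is not proved.

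- **Hospital care and medicines.** A reader might infer that these are not captured at all, the more so because the Discussion explains high costs by severity "as well as the need for general anesthesia or sedation". The documents do not support that. The fields for clinic type, procedure and total cost can hold a hospital dental procedure and its charge, and medicines supplied at a visit can fall within the total. Nor can the missed hospital cost be sized: the protocol gives neither a rate nor a cost of such episodes, and the whole cost of an episode is not the part the diary would lose.
- **Objective 3.** A reader might take its reference to associated expenditures to cover untreated toothache. The natural reading is expenditures associated with treatment. The ratio in *Cost-Effectiveness Analysis* also uses the difference in dental treatment cost, so days lost without treatment do not enter it as written. The mismatch is with the general societal statement.
- **Certain bias or a wrong sign.** A reader might infer either. Leaflets reach both arms and their content is not given, and children in both arms with obvious caries are advised to attend a clinic. The difference in attendance is therefore unknown, and the days lost per untreated child are assumed.
- **The form is not shown.** The diary is to be built from an existing cost questionnaire that may hold more items. This is fair for detailed lines, but it does not rescue the trigger: extra items on a form opened only at a clinic visit cannot record a day lost without one.

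The first three replies limit the point. They do not remove it, because the article states both the measurement rule and the perspective, and the two do not match.

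**Conclusion.** The point holds in a limited form. As stated, the diary measures the cost of dental clinic attendance, while the study claims a societal perspective with productivity loss. Losses without a visit are left out, and an inpatient stay has no listed place.

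The likely effect is to understate any societal saving from the home visits, since they encourage recorded attendance and are expected to reduce disease whose untreated burden is unrecorded. That direction is probable, not certain, and the size is unknown. Under the illustrative assumptions the missed saving is 0.09 day per child at 1 day per untreated child. A reversed sign is possible only in a band of added check-up attendance, 12 to 30 points at that value and narrower if fewer days are lost. This is a cheap improvement to data collection, not a flaw that invalidates the trial.

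**What to change.** Change the instruction to parents so that any dental problem or any dental care prompts an entry. Add lines for parent days off for a dental problem with or without a visit, care outside a dental clinic, medicines bought, and hospital stay. Have the researchers ask these same fixed questions in both arms at each existing 6-monthly diary check and at the 2-year visit.

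The article describes the diary as still to be created, translated and pretested, so this costs a few lines and a few minutes per visit. Recruitment is already under way; if diaries have been issued, the fixed questions can still be added at the scheduled checks. The downsides are a slightly longer diary and some recall error over 6 months.

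If this is not done, restate the perspective and the productivity claim as limited to costs of dental clinic attendance.
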